## Abstract

**Background:**

In the United States, most (~ 70%) annual newly diagnosed HIV infections are among substance-using sexual minority men (SMM) and gender minority transgender women (trans women). Trans women and SMM are more likely to report or be diagnosed with a substance use disorder (SUD) than their cisgender or heterosexual counterparts and the presence of an SUD substantially increases the risk of HIV infection in both groups. Although Pre-Exposure Prophylaxis (PrEP) is highly effective, initiation, adherence, and persistence are exclusively behavioral outcomes; thus, the biomedical benefits of PrEP are abrogated by substance use. SUD is also associated with reduced quality-of-life, and increased overdose deaths, utilization of high-cost healthcare services, engagement in a street economy, and cycles of incarceration.

**Objective:**

To determine the optimal (considering efficacy and cost-effectiveness) strategy for advancement along the PrEP Care Continuum among trans women and SMM with an SUD.

**Methods:**

This study will implement a randomized controlled trial, evaluating two Stepped Care approaches involving *A.S.K.-PrEP* vs. standard of care (SOC) to determine optimal intervention strategies for trans women and SMM with an SUD (*N* = 250; *n* = 83 trans women; *n* = 167 SMM) for advancement along the PrEP Care Continuum. Participants will be randomized (3:1) to Stepped Care (*n* = 187) or SOC (*n* = 63). Participants in the Stepped Care arm will be assessed at 3-months for intervention response; responders will be maintained in *A.S.K.-PrEP*, while non-responders will receive added attention to their SUD via Contingency Management (CM). Non-responders will be re-randomized (1:1) to either (a) receive *A.S.K.-PrEP* + CM, or (b) shift the primary focus to their SUD (CM alone).

**Results:**

Recruitment and enrollment began in May 2023. Recruitment will span approximately 36 months. Data collection, including all follow-up assessments, is expected to be completed in April 2027.

**Discussion:**

Trans women and SMM with an SUD have the two highest HIV prevalence rates in the United States, which underscores the urgent need for effective measures to develop scalable behavioral interventions that can encourage advancement along the PrEP Care Continuum. To improve public health, researchers must identify scalable and cost-effective behavioral interventions to promote PrEP initiation, adherence, and persistence among trans women and SMM who use substances.

**Trial registration:**

This trial has been registered at ClinicalTrials.gov under the number NCT05934877.

## Background

Tenofovir disoproxil fumarate/emtricitabine (TDF/FTC), tenofovir alafenamide/emtricitabine (TAF/FTC), and Cabotegravir to prevent HIV are highly effective when taken as prescribed [1]. In spite of this scientific advance, and scale-up of treatment efforts for persons with HIV (PWH) to reduce sexual transmissibility, the US still has ~ 35,000 annual HIV diagnoses, the majority of which occur among substance-using transgender women (hereafter: trans women) and sexual minority men (SMM) [2], groups that also evidence poor PrEP adherence. In the United States, trans women are the group at greatest risk for HIV, with an estimated HIV prevalence of 22–28% [3], while SMM have an estimated HIV prevalence of 15% [4]. These alarmingly high HIV prevalence rates constitute a call for action to determine scalable behavioral interventions to promote PrEP initiation, adherence, and persistence among trans women and SMM with a substance use disorder (SUD). A majority of trans women who initiate PrEP do not achieve prevention-effective adherence [5], that is sufficient biomarker-measured adherence required to achieve maximal levels of clinical HIV prevention, and similar outcomes are observed among high-risk SMM [6, 7]. Elevated seroconversion rates among trans women and SMM persist because, although PrEP is highly effective, PrEP initiation, adherence, and persistence – whether taking a pill or getting an injection – are exclusively behavioral outcomes that, by definition, mediate all biomedical benefits of PrEP; these benefits can be diminished in the setting of active use of stimulants and other substances [5, 7].

### Substance use impedes PrEP engagement among trans women and SMM

Numerous studies demonstrate that SUD is a major disruptor of medication adherence; whereas, reduced substance use is associated with increased medication adherence, and mitigation of HIV drug and sexual risk behaviors [8–10]. Among trans women and SMM, stimulant use in particular has been shown to interfere with PrEP initiation, adherence, and persistence [11–13]. Such findings are particularly concerning because trans women and SMM are not only more likely to report or be diagnosed with a current SUD than their cisgender or heterosexual peers [14, 15], but the presence of an SUD also substantially increases risk of HIV infection in both groups [16–18].

Trans women may face structural and interpersonal transmisogyny in the forms of mistreatment or hindered to access to opportunities and services [19, 20]. This can increase their risk of SUD and related health disparities, including housing instability and poverty [21, 22], engagement in sex work [23, 24], cycles of incarceration [25, 26], intimate partner violence [27, 28], sexual violence [29, 30], and mental health disorder(s) [30]. Low health literacy, sex work, and the experience of stigma or lack of gender-related social support are further known to increase medical mistrust and decrease HIV-related medication adherence and care engagement, especially in the presence of comorbid SUD [31, 32]. Similarly, SMM may experience structural and interpersonal forms of homophobia [33, 34], which may underlie SUD and comorbid housing instability [33], sexual violence [35, 36], physical violence [37, 38], mental health disorder(s) [15], and suicidality [39]. SUDs, mental health disorders, low health literacy, poverty, and traumatic stress have also all been shown to negatively affect HIV-related medication adherence among SMM [40, 41]. Due to these health disparities, evidence indicates that trans women and SMM exhibit poor knowledge and slow uptake of PrEP [42, 43], and when PrEP initiation does occur, suboptimal medication adherence is common [5, 7].

In general, SUD is associated with reduced quality-of-life, suboptimal utilization of primary and ambulatory care services, and increased overdose deaths, utilization of high-cost healthcare services (e.g., emergency department and inpatient encounters), engagement in the street economy, and criminal-legal activity [44–47]. The discounted average lifetime healthcare cost per United States PWH is estimated to be $368,000 (2020 USD), and healthcare costs have been shown to be 1.2–1.6 times higher for those with comorbid SUD [48]. The discounted average lifetime cost of non-healthcare SUD-related consequences (e.g., premature mortality, criminal-legal) could be an additional ~$2 million [47]. Thus, strategies that improve PrEP initiation, adherence, and persistence, as well as treatment for SUD, are critically important for personal, public, and national-economic health.

This study is a randomized clinical trial to evaluate the efficacy and cost-effectiveness of the Assistance Services Knowledge-PrEP (A.S.K.-PrEP) intervention, a PrEP navigation intervention with Short Message Service (SMS) support [49], embedded in a Stepped Care design that incorporates Contingency Management (CM) to reward improved SUD outcomes among non-responders. The overarching objective of the study is to determine the optimal (considering efficacy and cost-effectiveness) strategy for advancement along the PrEP Care Continuum among trans women and SMM.

## Methods

### Research aims

The specific objectives of the *A.S.K.-PrEP* study are to evaluate (1) a Stepped Care approach for promoting advancement along the PrEP Care Continuum (based on PrEP initiation, adherence, and persistence), and reductions in substance use, and (2) the cost-effectiveness of the *A.S.K.-PrEP* intervention in a Stepped Care approach with added attention to SUD, via CM, among trans women and SMM with an SUD (see Fig. 1).

**Fig. 1 Fig1:**
[figure not shown]
Schematic of ASK-PrEP Stepped Care, Randomized Controlled Trial Design

The trial will recruit 250 HIV-negative trans women and SMM with an SUD (*n* = 83 trans women; *n* = 167 SMM); participants will be randomized (3:1) to *A.S.K.-PrEP* (*n* = 187), or Standard of Care (SOC; PrEP education, information, and referrals) (*n* = 63). Participants in the *A.S.K.-PrEP* Stepped Care arm will receive 5 PrEP navigation sessions within 3 months and will be assessed at 3-months for intervention response; responders will maintain the *A.S.K.-PrEP* intervention, while non-responders will be re-randomized (1:1) to either add attention to their SUD (*A.S.K.-PrEP* + CM), or shift attention to their SUD (CM alone). The study uses repeated assessments at baseline and at 3-, 6-, 9-, and 12-months post-enrollment; all assessments will be administered to participants regardless of their participation or retention. All intervention content is tailored to trans women and SMM with an SUD. Participants may choose to initiate daily oral PrEP (TDF/FTC or TAF/FTC) or long-acting injectable Cabotegravir [10].

The specific aims of the research include the following:

#### Aim 1:

Evaluate the efficacy of a Stepped Care approach promoting advancement along the PrEP Care Continuum (initiation, adherence, persistence), and reductions in substance use among trans women and SMM with an SUD, relative to an SOC condition.

#### Hypothesis

*a*: Participants randomized to the *A.S.K.-PrEP* Stepped Care arm will achieve protective PrEP adherence, persistence, and reductions in substance use at greater rates over time, relative to participants in the SOC arm.

#### Hypothesis

*b*: Among participants randomized to the *A.S.K.-PrEP* Stepped Care arm, participants in arms containing CM will produce superior outcomes in PrEP adherence and persistence and greater reductions in substance use compared to participants in arms not containing CM.

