#### Contingency management (CM)

CM is a behavioral economics intervention that posits the application of contingencies to motivate individuals toward health-promoting behavior change [52, 53]. Behavioral economics incorporates direct and immediate reinforcement – the primary construct in the operant form of learning theory – whereby behaviors are learned through rewards. CM uses an operant reinforcement schedule that provides increasingly valuable rewards for consecutive urine samples that are nonreactive to the participant’s targeted SUD. As successive nonreactive urine samples are achieved and voucher points increase, so does one’s sense of self-efficacy to continue providing nonreactive urine samples.

At the 3-month follow-up assessment, non-responders (see Table 2) are stepped and re-randomized to CM, either in concert with *A.S.K.-PrEP* or alone. At the first CM session, a research assistant provides a 15-minute orientation to the CM procedures, which includes an explanation of the progressive, voucher-based reinforcement schedule. Thereafter, participants will meet with a research assistant thrice weekly to provide a urine sample. The CM protocol can be simplified into these guidelines: (1) participants receive a $2.50 voucher for the first nonreactive urine sample for their targeted SUD; (2) participants receive a voucher reflecting an incremental increase of $0.50 for each subsequent nonreactive urine sample; (3) participants receive a bonus of $7.50 for each 3 consecutive nonreactive urine samples; (4) vouchers are redeemable at any time for goods or services, selected by the participant, that support a healthy and pro-social lifestyle, such as groceries, camera equipment, clothing, bicycle; (5) participants who produce a urine sample that is reactive to their targeted SUD, or who fail to submit a urine sample, do not receive a voucher for that particular CM visit and their subsequent voucher value is reduced to the initial $2.50; and (6) a rapid reset procedure allows participants to return to their place in the escalating CM schedule after producing 3 consecutive nonreactive urine samples. Participants who complete the CM intervention without a reactive urine sample earn $495 in vouchers (see Table 3). If a participant is diagnosed with a SUD for two or more substances, they are asked, “Which drug do you use most despite negative consequences?” and that drug is targeted in the CM intervention.

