**Step Criteria Based on Substance Use**:
Self-reported drug use of the targeted SUD diagnosed at baseline for 1 (or more) day(s) in the past 14 days
Positive urine drug screen for targeted SUD diagnosed at baseline

**Table 3 Tab3:** Contingency management (CM) Voucher-based escalating reinforcement schedule

Week #	Mon	Wed	Fri	Bonus	Weekly Totals	Total Earned
**Week 1**	$2.50	$3.00	$3.50	$7.50	$16.50	$16.50
**Week 2**	$4.00	$4.50	$5.00	$7.50	$21.00	$37.50
**Week 3**	$5.50	$6.00	$6.50	$7.50	$25.50	$63.00
**Week 4**	$7.00	$7.50	$8.00	$7.50	$30.00	$93.00
**Week 5**	$8.50	$9.00	$9.50	$7.50	$34.50	$127.50
**Week 6**	$10.00	$10.50	$11.00	$7.50	$39.00	$166.50
**Week 7**	$11.50	$12.00	$12.50	$7.50	$43.50	$210.00
**Week 8**	$13.00	$13.50	$14.00	$7.50	$48.00	$258.00
**Week 9**	$14.50	$15.00	$15.50	$7.50	$52.50	$310.50
**Week 10**	$16.00	$16.50	$17.00	$7.50	$57.00	$367.50
**Week 11**	$17.50	$18.00	$18.50	$7.50	$61.50	$429.00
**Week 12**	$19.00	$19.50	$20.00	$7.50	$66.00	$495.00
**Maximum CM Payout**:						$495.00

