We quantify the primary intervention effects as the difference in proportion of participants who are adherent and persistent, comparing the Stepped Care intervention to SOC. We estimate this effect using longitudinal targeted minimum loss-based estimation (LTMLE) [67, 68]. This method appropriately accounts for the study design and the fact that only some participants are eligible for re-randomization, and accounts for predictive and prognostic time-varying participant-level covariates. Implementation of LTMLE involves estimating several sequential regressions modeling the probability of adherence and persistence as a function of time-varying covariates. In order to remove the potential for investigator bias in the analysis phase, we require that these regressions are fully defined a priori, which is challenging because model checking/re-fitting procedures cannot be employed while maintaining the study blind. Instead, we rely on the Super Learner for estimating these regressions [69]. The Super Learner is an ensemble machine learning approach that uses cross-validation to weight the contributions of several pre-specified candidate regression models. It can be used as a tool to pre-specify and fully automate the model selection process while remaining blinded to intervention assignments.

We study key secondary endpoints of PrEP initiation at 3-, 6-, 9-, and 12-months. PrEP initiation is operationalized dichotomously and is defined as confirmed acquisition of oral daily or long-acting injectable PrEP from a clinical provider. As with the primary analysis, we quantify treatment effects in terms of differences in probabilities of initiation and assess them via LTMLE and Super Learning.

Cumulative days of substance use are measured via TLFB, and urine drug screens, with the focus being the participant’s primary substance of concern. Self-reported substance-free days must be confirmed by non-reactive urine drug screen results; missing urine drug screens are treated as positive, consistent with the SUD literature [70]. We quantify treatment effects in terms of the difference in average cumulative days of substance use at 3-, 6-, 9-, and 12-month follow-up visits. The secondary substance use outcomes include the cumulative: (a) proportion of positive urine drug screens at 3-, 6-, 9-, and 12-months [71]; and (b) days of self-reported substance use at 3-, 6-, 9-, and 12 months. These analyses also leverage LTMLE and Super Learning.

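### Hypothesis b compares Stepped Care with CM against Stepped Care without CM, but only 3-month responders go without CM, so the design cannot identify the comparison

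*Protocol article*

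**What the plan says.** Protocol article, Research aims, Hypothesis b under Aim 1, is limited to participants randomised to Stepped Care. It states that those in arms with CM will have "superior outcomes in PrEP adherence and persistence and greater reductions in substance use compared to participants in arms not containing CM".

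The design is described consistently elsewhere:

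- Abstract, Methods: "responders will be maintained in *A.S.K.-PrEP*, while non-responders will receive added attention to their SUD via Contingency Management (CM".
- Abstract, Methods, on the second randomisation: "Non-responders will be re-randomized (1:1) to either (a) receive *A.S.K.-PrEP* + CM, or (b) shift the primary focus to their SUD (CM alone".
- Interventions, Contingency management: non-responders "are stepped and re-randomized to CM, either in concert with *A.S.K.-PrEP* or alone".
- Table 2 bases the step decision on PrEP (not started, self-reported gap in oral dosing, late second injection) and on substance use (recent self-reported use, or "Positive urine drug screen for targeted SUD diagnosed at baseline").
- Statistical analysis/outcomes, Specific Aim 1, expresses the primary effect as a difference in proportions, "comparing the Stepped Care intervention to SOC". The power statement likewise covers intervention against SOC only.

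**The concern.** Hypothesis b reads as a test of what CM contributes, but the design gives it no valid comparator. Within Stepped Care, receiving CM is the same thing as having been a non-responder at 3 months. The two sides are sorted by an early form of the outcomes on which they are then compared.

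A reader of the results could take the comparison as evidence about CM when it mainly shows that early responders and early non-responders differ. Meanwhile the contrast that the second randomisation does support, A.S.K.-PrEP + CM against CM alone, has no Aim 1 hypothesis on adherence, persistence or substance use.

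**Working it through.** **The plan's own figure.** The protocol states at least 80% power for a 20-point difference, intervention against SOC. For 187 against 63, two-sided 0.05, no attrition, and assumed SOC rates of 10, 20, 30, 40 and 50%, power is 93.5, 84.9, 80.2, 79.2 and 81.4%. The statement is reproduced to within rounding. It concerns Stepped Care against SOC and says nothing about Hypothesis b.

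**Who is on each side of Hypothesis b.** Of the 187 in Stepped Care:

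| 3-month status | Assigned to | Contains CM? |
|---|---|---|
| Responder | A.S.K.-PrEP continued | No |
| Non-responder | A.S.K.-PrEP + CM | Yes |
| Non-responder | CM alone | Yes |

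So P(CM | responder) = 0 and P(CM | non-responder) = 1. The two sides do not overlap on response status. LTMLE needs some chance of each option at each relevant history. Here that chance is zero, so covariate adjustment could only extrapolate.

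**Size of the bias.** Let p0 be later adherence in non-responders without CM, d the true CM effect in them, and pR later adherence in responders.

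- Observed contrast = (p0 + d) − pR
- Bias = p0 − pR
- The sign reverses when pR − p0 exceeds d.

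The documents give none of these rates. With d = 20 points (assumed):

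| p0 | pR | Observed | Bias |
|---|---|---|---|
| 20% | 50% | −10 | −30 |
| 20% | 60% | −20 | −40 |
| 20% | 70% | −30 | −50 |
| 30% | 40% | +10 | −10 |
| 30% | 30% | +20 | 0 |

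A simulation (400,000 participants per scenario) let one latent tendency drive both 3-month response and later adherence, again with d = 20 points:

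| Latent SD (logits) | Observed if response needs both domains | Observed if response is PrEP only |
|---|---|---|
| 0.5 | +13 | +15 |
| 1.0 | −1 | +4 |
| 1.5 | −14 | −8 |
| 2.0 | −25 | −18 |

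The bias (observed minus 20) runs from about −5 to −45 points. It vanishes only if 3-month response does not predict later outcome.

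**Precision of the randomised contrast.** n per arm = 187 × non-response proportion / 2. Detectable difference at 80% power = 2.8 × √(0.5/n), the most conservative variance, before attrition. Power for 40% against 60% is Φ(0.20/√(0.48/n) − 1.96).

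| Non-response (assumed) | n per arm | Detectable difference | Power, 40% vs 60% |
|---|---|---|---|
| 60% | 56 | 26.4 points | 58% |
| 70% | 65 | 24.5 points | 65% |
| 80% | 75 | 22.9 points | 70% |
| 90% | 84 | 21.6 points | 75% |

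**Embedded strategies.** Both strategies share the same responders, so the between-strategy difference = non-responder difference × non-response proportion. A 20-point difference in non-responders becomes 20 × 0.6 = 12 to 20 × 0.9 = 18 points.

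**The case against.** The strongest reply is that the article specifies no naive test of Hypothesis b. Its analysis text fixes Stepped Care against SOC, says that LTMLE accounts for restricted re-randomisation, and may leave the rest to an analysis plan not shown. That stands as far as it goes: a reader might infer that the trial will report CM as harmful, and the documents do not show that such an analysis will be run. It does not rescue the hypothesis, because no analysis plan can supply a no-CM option that no Stepped Care non-responder was assigned. SOC cannot fill the gap either: Hypothesis b excludes it, and it lacks A.S.K.-PrEP too.

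Second, a reader might infer that the trial's question about the optimal strategy goes unanswered. That is too strong. Aim 2 compares the two stepped strategies with SOC and with each other on costs, QALYs and PrEP Care Continuum steps, and Hypothesis 2 predicts their order. What is missing is an Aim 1 hypothesis for that contrast on adherence, persistence or substance use.

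Third, a reader might infer strong bias against CM on every outcome. The documents give no response or outcome rates, so the size is unknown. If substance-use reduction were measured from month 3, responders would start near the floor and the bias could favour CM.

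Fourth, Table 2 does not say which combination of criteria triggers stepping, so responders cannot be assumed to have passed all of them. The confounding holds under any combination.

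**Conclusion.** Hypothesis b is wrong as written. Its comparison is non-randomised, confounded by 3-month response, and not identifiable in this design. This conclusion follows from the allocation rules alone and needs no assumed rates.

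The size does need them. For adherence and persistence the expected direction is against CM, and a true benefit could change sign (+20 shown as −20 in the central illustration). With weak dependence between early response and later outcome the bias is only a few points. For substance use the direction is open.

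Hypothesis a, the 3:1 comparison with SOC and its power statement are unaffected.

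**What to change.** 1. Restate Hypothesis b as A.S.K.-PrEP + CM against CM alone among re-randomised non-responders. State that this estimates the value of keeping navigation alongside CM, not of adding CM.
2. Alternatively, or in addition, compare the two embedded strategies with each other and with SOC using the planned LTMLE. Name this as a separate estimand. It is not interchangeable with item 1, because the between-strategy difference is diluted by the responders that both strategies share.
3. State that CM against no CM in non-responders is not estimable, and present any responder against non-responder comparison as descriptive only.
4. Report the precision for the non-responder contrast: a detectable difference of about 26 to 22 points at 80% power, if 60 to 90% of 187 are non-responders (assumed, before attrition). These figures do not apply to the strategy-level contrast.

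The cost is one reworded hypothesis, one added analysis, and a stated precision less favourable than the 20 points given for the comparison with SOC. No new data are needed.
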